### Data collection methods

The patients in both arms will be asked to attend after 3 months (90 days ± 15 days) for a follow-up interview to assess adherence and health literacy. Data will be collected on a data collection form (DCF) by a research officer who is blinded to participant allocation. This primarily consists of the MMAS and modified TOFHLA. In addition, in a select sample of patients, the research officer will also perform pill counts every 2 weeks. (Additional file 2 − Data Collection Form).

Participants in both arms will be reminded of their appointment 2 days prior to the interview. Patients will be compensated for travel to AKUH for the 3-month follow-up visit. In case the participant does not report for this appointment, they will be contacted again to reschedule it.

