## Methods

### Design overview

The *Bolta Parcha* (Talking Prescription; Talking Rx) trial is a randomized, controlled, single center superiority trial with blinded outcome assessment. (Fig. 1 – Study flow chart) Adult participants, with access to a cell phone and a history of vascular disease longer than 1 month of duration, who are taking multiple risk-modifying medications (inclusive of anti-platelets and statins) will be selected from neurology and stroke clinics at the AKUH.

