##### Pill count

On a select sub-set of the intervention group (approximately 20 %) medication adherence will be objectively monitored by doing a pill count. Selected patients are provided with two weekly pill organizers each and their anti-platelets and statins are filled in these organizers for 2 weeks. The patient is then asked to return every 2 weeks for a pill count to objectively assess medication adherence as a direct measure of the intervention being provided to these patients via SMS and Talking Prescription. These patients are required to visit the facility for a pill count every 2 weeks until the cessation of the study (i.e., 3 months).

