If there is a change in patient prescription with respect to any drug or dose by any physician, the patient will be requested to notify this on a helpline number that is provided to them during enrollment. In addition, there is a fortnightly review by a research officer to screen and ensure safety and to draw attention to any prescription change that has not been noticed. This allows the Talking Prescription to be modified so that the patient can then be sent instructions according to the new regimen. The helpline is available round the clock and it could also be reached in the case of any queries. The operator at the helpline is trained to answer and deal with most frequently anticipated questions and queries and is given access to a stroke neurologist and a cardiologist at all times in case of queries beyond the scope of their knowledge. If it is anticipated that the participant will undergo frequent medication changes, associated with, e.g., planned carotid endarterectomy (CEA), CABG, stent, etc., they are not enrolled into the program until their condition is stable.

Following the recruitment visit, the patients will not be required to come back to clinic for any additional visits except the end of the study visit at 3 months. The only exception to this will be the select sub-set which is selected for a pill count, which have a fortnightly review. At the end of the study, patient adherence and health literacy is assessed by the research officer who is unaware of patient allocation. (Fig. 3 − Participant timeline for Talking Rx).

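### The blinded 3-month assessor is also assigned the fortnightly pill counts, which one section confines to the intervention arm, so blinded assessment is not secured for that subset

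*Protocol article*

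**What the plan says.** All places are in the Methods of the protocol article.

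- **Design overview** describes a "single center superiority trial with blinded outcome assessment".
- **Data collection methods** has the 3-month data, mainly MMAS and modified TOFHLA, collected "by a research officer who is blinded to participant allocation". Later in the same paragraph it adds that "in a select sample of patients, the research officer will also perform pill counts every 2 weeks".
- **Study timeline** repeats that adherence and health literacy at the end of the study are "assessed by the research officer who is unaware of patient allocation".
- **Pill count**, a subsection under Intervention group, opens "On a select sub-set of the intervention group" and gives the share as about 20 %. It describes the count "as a direct measure of the intervention being provided to these patients via SMS and Talking Prescription".
- **Design overview**, in the text after Fig. 1, gives a different subset: 20 % of the patients in each group.
- **Study timeline** also states that "there is a fortnightly review by a research officer to screen and ensure safety and to draw attention to any prescription change", and that this lets the Talking Prescription be updated. Only the intervention arm has a Talking Prescription.

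**The concern.** The primary outcome is self-reported adherence collected at interview from participants who know their arm. The Discussion names self-report as the major limitation and the lack of participant blinding as another, and it lists blinded assessment among the design's strengths. Assessor blinding is therefore one of the main protections left on the primary comparison.

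That protection is weakened if the person who runs the 3-month interview has already seen the participant every two weeks for a procedure done in one arm only. An assessor who knows the arm may probe, prompt or record differently, and this would add to any self-report bias already present. The same interview yields the secondary outcome, so the exposure is shared.

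**Working it through.** The plan gives no figure for this point, so there is none to reproduce. The check sets the passages side by side and then scales the consequence against the plan's own target effect.

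**Step 1: Is the pill counter the blinded assessor?** Data collection methods introduces a blinded research officer and then, in the same paragraph, refers to the research officer who will *also* count pills. The definite article and the word "also" point back to the blinded interviewer. No section assigns the count to anyone else.

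**Step 2: Does the count reveal the arm?** This depends on which description of the subset governs. With 100 patients per arm (Sample size) and a 20 % share:

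| Source | Subset | Pill-count patients | Chance that a pill-count patient is on intervention |
|---|---|---|---|
| Pill count section | intervention group only | 0.20 × 100 = 20 | 20/20 = 100 % |
| Design overview | 20 % of each group | 0.20 × 200 = 40 | 20/40 = 50 % |

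Under the Pill count section the arm is known for certain for about 20 patients. Under the Design overview the count carries no information about the arm. The mention in Data collection methods, and the one in Study timeline, do not restrict the subset by arm and so do not settle the matter.

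**Step 3: Is there exposure even under the Design overview version?** Follow-up is 90 days with a count every 14 days: 90/14 ≈ 6.4, or about six contacts. Participants are not blinded, and those on intervention receive daily messages. Disclosure in conversation is a realistic risk, but the documents give no basis for a rate.

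**Step 4: Is the prescription review a second route?** Whoever uses the review to update a Talking Prescription learns that the patient is on intervention. Study timeline gives the review to *a* research officer and the final assessment to *the* officer unaware of allocation. The job title is shared. Identity of the person is neither stated nor excluded.

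**Step 5: Illustrative size.** If the assessor's knowledge shifts MMAS by *b* points in a fraction *f* of the intervention arm, the arm mean shifts by *f* × *b*. With *f* = 0.20 and an assumed *b*:

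- *b* = 0.25: 0.20 × 0.25 = 0.05 points
- *b* = 0.5: 0.20 × 0.5 = 0.10 points
- *b* = 1: 0.20 × 1 = 0.20 points

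Against the 1-point difference in Sample size, that is 5 % to 20 % of the target. The values of *b* are assumptions, and so is the direction of the lean.

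**The case against.** The strongest reply is that only one section limits pill counts to the intervention arm. If the Design overview is correct, the count itself reveals nothing. That stands, and it means that the conflict between the two sections is part of the problem. It does not remove the problem, because the Pill count section is the detailed operational description, and staff who follow it would unblind the assessor.

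A second reply is that the protocol states assessor blinding repeatedly and does separate roles. Study staff step out before allocation, the Clinical Trials Unit randomizes, and an unblinded investigator demonstrates the intervention. This is true, but these safeguards operate at enrollment, whereas the pill counts run through follow-up. Finer staff delegation can be left to a full protocol. Here, however, the article itself makes the assignment that causes the difficulty.

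A third reply is that the MMAS has eight fixed items scored 0 or 1, which limits an interviewer's latitude. This is fair, and it argues for the lower part of the illustrative range.

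A reader might also infer that the prescription review unblinds the assessor for all 100 intervention patients. The documents do not support that:

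- No section says that the reviewer is the assessor, and research officers are mentioned in the plural.
- The review also has a safety purpose and is not restricted to one arm.
- It need not involve patient contact. Study timeline requires no visits before 3 months except for the pill-count subset, whose visits it also calls a fortnightly review.

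**Conclusion.** The point holds for the pill-count subset. Data collection methods and the Pill count section, followed as written, would let the 3-month assessor know the arm of about 20 of 100 intervention patients, contrary to the blinding stated in Design overview and Study timeline. If the each-group description governs, direct unblinding disappears and what remains is the risk of disclosure over about six contacts.

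The illustrated shift of 0.05 to 0.20 points rests on an assumed lean of 0.25 to 1 point confined to 20 % of the intervention arm. It is not an estimate. It would be tempting to conclude that blinded assessment fails across the trial, with a bias approaching the full lean. That conclusion needs the assessor to perform every prescription review, which the text does not say. The supportable conclusion is that blinding is not secured, and that the prescription review is a possible further route to be closed.

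**What to change.** 1. Reconcile Design overview and Pill count, so that both describe a subset drawn from both arms, as Design overview already does.
2. Change Data collection methods so that pill counts are done by staff other than that participant's 3-month assessor, for example the investigator who is already unblinded.
3. State that the 3-month assessor does not carry out the prescription review or use the Talking Rx application for that participant.

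The cost is a few sentences and a small scheduling burden from reassigning tasks among existing roles. Staff numbers are not given, so the burden cannot be stated more exactly. If the site had been working to the intervention-only description, drawing from both arms also adds pill organizers and fortnightly visits for about 20 control participants (0.20 × 100).

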### Pilot testing

Pilot Testing was performed on 10 % of the sample size, i.e., 20 patients before commencement of the study. As per the actual study, participants were recruited from neurology and cardiology clinics and standard procedures are followed. This allowed testing the intervention for smooth application and any systematic errors. Problems with eligibility criteria were identified and the feasibility of achieving sample size was assessed. The data collection tool was also assessed for flow of questions and comprehensiveness. The intervention was assessed for practicality relating to delivery, accuracy, timeliness, comprehension and satisfaction. The participants in the pilot testing are excluded from final study analysis.

### Data management

Research officers are specifically trained to collect all data during patient interviews leaving no data collection forms incomplete. All data collected will be sent to the research office in sealed envelopes. At the end of each day any data missing from forms will be noted and asked for. In case of missing data, the participant will be contacted to fill the missing information. The data will be entered by a separate team which will enter data on EpiData. Data entry is depersonalized with study ID assignment. This team does not include any members involved with research. As per institutional policy, double entry is mandatory for all data. The data entry operators are blinded to the allocation of each patient. All data entered is backed up centrally.

### Statistical methods

Analysis will be performed using the intention-to-treat principle: an interim analysis after 25 % of the sample has been reached and final analysis after data has been collected from all study participants. Since this is an IT-based intervention, we plan to do an interim analysis to assess technical compliance to intervention, any unexpected side effects like participant fatigue and drop out. We do not expect any serious safety issues to arise as this study only concerns reception of educational intervention.

The use of the intention-to-treat principle for analysis means that all patients will be analyzed in the treatment arm to which they were randomized. Analysis will be performed after the completion of follow-up of all study participants. Protocol deviations and exclusions (with reasons, will be reported for each arm of the trial). Estimates of intervention effects will be presented with 95 % confidence intervals. A two-tailed *P* value of ≤0.05 will be considered statistically significant for the outcome measures.

For descriptive analysis, mean with standard deviation or median with interquartile range will be reported for continuous data. For categorical data, frequency with percentages will be calculated.

The primary outcome analysis will be based on improvement in medication adherence level, assessed by the change in MMAS score at 3 months of follow-up. To report the difference between the mean scores of intervention group and control arm, Student’s *t* test or the Mann-Whitney *U* test will be performed.

To evaluate the secondary outcome, change in functional health literacy assessed by TOFHLA, the difference of proportion between the two arms will be calculated either by Pearson’s chi-square test or Fisher’s exact test.

To evaluate the correlation between adherence to medications and pill counts either Pearson’s correlation or the Spearman rank correlation test will be applied and coefficients will be calculated to report the strength of correlation.

All analysis will be performed on Stata version13.

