### Outcomes: (Additional file 2 − Data Collection Form)

The primary outcome of interest is a change in medication adherence after 3 months of receiving the SMS and being exposed to the Talking Prescription (*Bolta Parcha*). Our secondary outcome is change in health literacy. The findings of the treatment group on these outcomes will be compared to the corresponding findings from the control group to account for the Hawthorne effect.

Medication adherence will be measured at recruitment and after 3 months in both groups using the MMAS. The scale has been used in a similar setting previously and it has been translated and validated in Urdu. The change will be determined by comparing the score on the MMAS before and after the intervention [15].

The instrument consists of eight questions and the response to each question is scored as either 0 (yes) or 1 (no). The maximum score, hence, is 8. A higher score indicates better adherence. A score of less than 2 indicates low adherence.

The secondary outcome measure is assessment of functional health literacy in adults (TOFHLA) which will be assessed at enrollment and then at the follow-up visit after 3 months. This tool has been adapted, modified, and content-validated by a panel of experts, translated and back-translated from English to Urdu, to better represent the Pakistani community and its health system. It consists of two sections: the first section covers questions about the basic instructions for each patient coming to the clinic, and the second section contains three passages comprised of questions about the relevant information every patient visiting the hospital should ideally possess.

Section 1 has a total of 17 questions, where a correct answer merits a score of 1 and an incorrect answer gets a score of 0. First Raw score is obtained after adding responses to each question and this score out of 17 is converted to a weighted score, using a reference table, to a denominator of 50.

Section 2 has a total of 50 questions, where each correct answer earns a score of 1 for the patient and an incorrect answer earns a score of 0. The total score at the end of this section is scored out of 50.

In the end, TOFHLA is evaluated on a total of 100, where health literacy is given a total score ranging between 0 and 59 (inadequate), between 60 and 74 (marginal), and from 75 up to 100 (adequate) [8].

In addition, we will perform sensitivity analyses comparing the correlation between the MMAS and the pill count.

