### Study timeline

Prior to each stroke/cardiology clinic visit, potential study participants will be identified from the clinic appointment lists. These patients, along with all other walk-in patients, will be approached by research officers during their visit to assess their eligibility for participation through an eligibility questionnaire. Those found eligible are informed about the study and if willing, will be requested to remain after their appointment for recruitment and providing written, informed consent. If a participant is interested but does not have time, they will be offered information about the study and asked to consider participation in the study at their next clinic visit.

First, counseling is performed by a research officer, in which details of the study, its purpose, objective, procedure and its follow-up visits are explained to the eligible participant. Recruitment will begin with signing of an informed consent and assigning the patient an ID number. Data collection will begin with a detailed interview regarding the demographic and clinical details of the patient including his/her prescription details. The baseline MMAS and TOFHLA scores for each patient will then be assessed. This will be followed by the research staff leaving the room and a senior investigator taking over, at which point the patient will be randomized to either the intervention or the control group by the CTU. The tasks of allocation of intervention and randomization are carried out by the CTU staff (separate from the study staff) and are independent from all studies that are ongoing at the university site.

If the patient is allocated to the intervention arm, the investigator will explain the details of the intervention. The investigator will also demonstrates it by sending one test SMS on his/her cell phone (in English and Urdu both). Any questions pertaining to the use and comprehension of IVR or SMS will be answered at that point.

Patients in the intervention arm will then be provided with a number on which they can dial (free-of-cost) the Talking Prescription. The unblinded investigator will then demonstrate this call to the participant and provide orientation regarding proper use of this IT facility.

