### Sample size

The sample size was calculated to detect a difference of 1 point on the primary outcome measure, MMAS, with a power of 90 % and significance level of 5 % between the two groups. The estimated sample size for the study is 86 participants in each arm. Accounting for a 15 % attrition rate the minimum sample size required for the study is 100 participants per arm, making a total of 200 participants to be randomized. The MMAS categorizes low adherence as a score of <6, medium adherence as a score of 6 to <8, and high adherence as a score of 8 [16]. Any 1-point shift is a clinically important increase in scores. In addition, in a study carried out locally, we have shown the use of IT-based interventions to have effects on this score in these ranges [17, 18].

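### The primary analysis should be one named test adjusted for baseline MMAS, not an unadjusted t test or Mann-Whitney test on change: a gain in precision and clarity, not the repair of an invalid test

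*Protocol article*

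**What the plan says.** Under Statistical methods, the primary analysis rests on improvement in adherence, "assessed by the change in MMAS score at 3 months of follow-up". The stated purpose of the comparison is this: "To report the difference between the mean scores of intervention group and control arm". Two alternative methods, Student's t test and the Mann-Whitney test, are then offered for it. No covariate is named, and nothing says what decides between them. The same section promises intervention effects with 95 % confidence intervals and a two-tailed 5 % level.

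Baseline data are complete by design. Under Outcomes: "Medication adherence will be measured at recruitment and after 3 months in both groups using the MMAS". Study timeline places this before allocation: "The baseline MMAS and TOFHLA scores for each patient will then be assessed", after which the patient is randomized. The scale is bounded; Outcomes says "The maximum score, hence, is 8".

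Under Sample size: "The sample size was calculated to detect a difference of 1 point on the primary outcome measure, MMAS". The power is set at 90 % and the significance level at 5 %, which leads to 86 evaluable participants per arm. No SD is given. The section does not say whether the 1 point refers to change or to the 3-month score.

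**The concern.** Two features of the primary analysis deserve attention.

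First, precision. Subtracting the baseline amounts to assuming that the 3-month score rises by a full point for each baseline point. When the correlation between visits is below 1 and the variances are similar, the true slope is smaller, so subtraction puts baseline noise into the comparison. Estimating the slope instead removes that noise. Any chance baseline difference between arms also enters the change score through regression to the mean. Assignment of interventions describes blocks of 10 and no stratification, so nothing in the design balances baseline adherence.

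Second, the open pair of tests. The stated aim is a difference in means with a confidence interval, and the trial is sized on such a difference. Mann-Whitney compares ranks and supplies neither. If it is used, the significance statement and the reported interval come from different methods and could disagree. With no rule in the text, the choice could also be made after the data are seen.

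At stake are the width of the interval for the main result and whether its p-value and interval tell the same story.

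**Working it through.** **Inputs from the article.** Difference 1 MMAS point, power 90 %, two-sided 5 %, 1:1 allocation, 86 evaluable per arm. **Assumed, because not given:** the SD, and the correlation rho between baseline and 3-month MMAS, taken as 0.3 to 0.7.

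**Step 1: the plan's own figure.** Without an SD, 86 cannot be rebuilt from the stated inputs alone. Solving backwards by the normal approximation, SD = sqrt(86/2)/(1.960 + 1.282) = 6.557/3.242 = 2.02. Going forwards with SD 2.0, the normal formula gives 85 per arm, and the noncentral t solution gives 85.03, rounded up to 86. So 86 fits an unadjusted two-sample comparison with an SD of about 2.0.

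**Step 2: variances.** Let s0 and s1 be the SDs at baseline and 3 months.

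- Change score: s0² + s1² − 2·rho·s0·s1
- ANCOVA residual: s1²(1 − rho²)
- Difference: (s0 − rho·s1)², which is never negative

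So, apart from the one degree of freedom spent on the slope, ANCOVA is never less precise, whatever the two variances. If s0 = s1 = s, the variances are 2s²(1 − rho) and s²(1 − rho²), with ratio (1 + rho)/2.

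| rho | ANCOVA/change variance | Interval width ratio (square root) | 86 per arm acts like |
|---|---|---|---|
| 0.3 | 0.65 | 0.81 | 86/0.65 = 132 |
| 0.5 | 0.75 | 0.87 | 86/0.75 = 115 |
| 0.7 | 0.85 | 0.92 | 86/0.85 = 101 |

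At rho = 0.9 the ratio is 0.95, a gain of only 5 %.

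**Step 3: power at 86 per arm** (normal approximation, difference 1, equal variances). The result depends on what the SD of 2.0 describes.

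| rho | A: 2.0 is SD of change; t on change | A: ANCOVA | B: 2.0 is SD of a single score; t on change | B: ANCOVA |
|---|---|---|---|---|
| 0.3 | 90.6 % | 98.2 % | 79.1 % | 93.0 % |
| 0.5 | 90.6 % | 96.6 % | 90.6 % | 96.6 % |
| 0.7 | 90.6 % | 94.5 % | 98.8 % | 99.6 % |

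Under B the SD of change is 2.0·sqrt(2(1 − rho)). This exceeds 2.0 exactly when rho is below 0.5; at rho = 0.3 it is 2.0·sqrt(1.4) = 2.37. Under A the planned power is as stated.

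**Step 4: the open choice of test.** A null simulation used assumed normal scores (mean 6, SD 2, rho 0.5) rounded and cut to 0 to 8, with 86 per arm and 6,000 runs. Type I error was 5.2 % for the t test, 5.4 % for Mann-Whitney, 5.4 % when a Shapiro-Wilk check decided between them, and 6.5 % when the smaller p-value was always reported. Simulation error is about sqrt(0.05 × 0.95/6000) = 0.3 percentage points.

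**The case against.** The strongest reply is that nothing here is invalid. Under 1:1 randomization a t test on change is unbiased, and chance baseline differences average out over randomizations. That stands: the loss is one of efficiency.

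A reader might infer from the 79 % figure that the trial misses its 90 % power. The article does not support this. The figure needs both that the implied SD describes a single score and that rho is below 0.5, and neither is given. Since the primary outcome is defined as change, the implied SD may equally be that of change, in which case the planned power holds.

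A reader might also infer that the unstated choice of test seriously inflates the false-positive rate, or that the estimand itself shifts with the test. Neither follows. The inflation is modest even when the smaller p-value is always taken, and negligible when a distributional check decides. An article may leave such a rule to a fuller document that is not shown. The text names a difference in means as the target whichever test is used, and a mean difference with its interval can be reported beside a rank-test p-value. What remains is that the two might not correspond.

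Finally, the factor (1 + rho)/2 needs equal variances at the two visits. Scores pushed towards the ceiling of 8 could change the 3-month variance and so the size of the gain. That also stands. By Step 2 it does not reverse the direction.

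**Conclusion.** The point holds as a recommended improvement, not as an essential correction. The article itself fixes an unadjusted comparison of change by one of two tests while baseline MMAS is available for everyone, so this is more than detail left to an analysis plan. Adjusting for baseline would cut the variance by about 15 to 35 %, and the interval width by about 8 to 19 %, for rho of 0.7 to 0.3. This assumes equal variances and a correlation that the article does not state. The 90 % power claim is neither confirmed nor refuted. In every scenario tabulated, ANCOVA exceeds 90 %. Naming one model also ensures that the p-value and the confidence interval refer to the same mean difference, the quantity on which the trial is sized.

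**What to change.** Replace the sentence on the primary test with one along these lines: the primary analysis is a linear model of the 3-month MMAS score on arm, adjusted for baseline MMAS, with robust standard errors; the adjusted mean difference is reported with its 95 % confidence interval and the p-value from the same model. Keep Mann-Whitney on the change score as a named sensitivity analysis.

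The outcome need not be redefined. Modelling change with baseline as a covariate gives the same arm coefficient as modelling the 3-month score with baseline as a covariate. Robust standard errors are advisable because the scale is discrete and bounded. Clinic (stroke or cardiology) may be added as a covariate but is not required, since the article describes no stratification by clinic.

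No new data or visits are needed. The trial is listed as ongoing, so the cost is the amendment route under Ethics and human subjects' protection: ethics committee approval before implementation, and a report to the registry. This should be done before any comparison by arm is seen, ideally before the interim analysis at 25 % of the sample.
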